## **2. Analysis Software**

Statistical analysis will be performed by independent analysts by R (version 4.1.0; R Development Core Team) software. All hypothesis testing will be carried out at the 5% (2-sided) significance level.

## **3. Missing Data**

Missingness is considered to be missing at random (MAR) and multiple imputation (MI) techniques will be used for handling missing data.

## **4. Analyses for Baseline Analysis**

Baseline information includes: Age; BMI(Prepregnancy); Race; ABO blood groups; Rh blood types; Place of residence; Educational level; Occupation category; History of tobacco consumption; History of alcohol intake; Insurance; Age of menarche; Menstrual cycle; Menstrual phase; Dysmenorrhea; Marital status; Couple relationship; Mode of conception; Prenatal care; Pregnancy complications; Fetus and appendages; Sleep duration per day; Trouble falling asleep; Appetite; Little interest or pleasure in doing things; Feeling down, depressed, or hopeless; Feeling nervous, anxious or on edge; Not being able to stop or control worrying; Labor induction; Augmentation by oxytocin; Rupture of membranes; Spinal analgesia for labor pain; Duration of labor stages; Perineum conditions; Assisted vaginal delivery; Placenta delivery method; Completeness of placenta; Fetal membranes; Curettage; Uterotonics drugs; Bowel movement during labor; Gestational age of delivery; BMI(Predelivery); Newborn weight; Newborn length; Apgar score; Time between birth and early sucking of newborns; Knowledge of breastfeeding; Postpartum diet within 28 hours after delivery; Postpartum diet during 28-52 hours after delivery; Postpartum diet during 52-76 hours after delivery; Postpartum appetite within 28 hours after delivery; Postpartum appetite during 28-52 hours after delivery; Postpartum appetite during 52-76 hours after delivery.

For continuous variables, means and standard deviations(SD) will be presented, unless the variable has a skewed distribution, in which case medians, 25th and 75th percentiles will be presented. For categorical variables, the number and percentage of participants within each category will be presented. For each variable (continuous or categorical), the number of missing values will be reported. Continuous data will be analyzed using the t test or Wilcoxon rank-sum test. Categorical data will be analyzed using the chi-square test or Fisher's exact test.

## **5. Analyses for the Primary Outcome**

For the primary outcome, comparisons of urinary retention between intervention group and control group will be performed using logistic regression model without any adjustment; relative risk (RR) and corresponding 95% confidence intervals(CIs) will be calculated.

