**Figure 2. Trial flow chart**

## 2.3.4 Recruitment

The study will be conducted in 12 hospitals in China: Women's Hospital, School of Medicine, Zhejiang University; Tongde Hospital of Zhejiang Province; Yiwu Maternity and Child Health Care Hospital; Jiaxing Maternity and Child Health Care Hospital; Zhejiang Xiaoshan Hospital; Zhoushan Women and Children Hospital; Shaoxing Maternity and Child Health Care Hospital; The Women & Children Hospital of Dongyang; Ruian People's Hospital; Cixi Maternity and Child Health Care Hospital; Wenling Maternity and Child Health Care Hospital and Xianju People's Hospital. Posters will be placed in each institution's bulletin board to recruit subjects. No specific culture, race, or socio-economic group will be targeted or restricted from the recruitment.

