## **2.4 Sample size calculation**

This study will use a superiority design. According to the pilot study, the incidence rate of urinary retention was 7.7% in the intervention group and 25.7% in the control group. Assuming a 1 : 1 ratio of intervention to control group and using a one-sided test, a significance level ( $\alpha$ ) of 0.025 and a power ( $1-\beta$ ) of 80% and a possible drop-out rate of 20%, the estimated sample size is 600 cases in each group with 50 cases at each center in each group. Intervention and control groups would require a total sample size of 1200 cases.

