## 11. Update on the Published Protocol

As compared to the published protocol ([name], [name], Chang Liu, Nicola Robinson, Myeong Soo Lee, Xiaoyang Mio Hu, Hye Won Lee, Rong Zhang, [name]\*. Effectiveness of acupoint hot compress on early puerperal rehabilitation of parturients after natural childbirth: study protocol for a prospective, multi-center, randomized controlled clinical trial. *Clinical and Experimental Obstetrics & Gynecology*.2021;48(6):1350-1357), the present study protocol has made several amendments.

- (1) The medical provision of two centers changed, which has limited the number of the available participants with inclusion criteria of the study, and these two centers were not included in the trial.
- (2) The analysis used in the present trial is referred to as an “per protocol” analysis.
- (3) To detect the effects of acupoint hot compress on reducing the incidence of urinary retention more accurately, we used a broader standard to identify postpartum urinary retention.
- (4) To detect the effects of acupoint hot compress on lactation, we used a detailed measurement to quantify the breastfeeding milk volume.
- (5) As all the outcomes collected from 6±0.5 hours to 76±0.5 hours after delivery, the changes of maternal weight is tiny, so the weight was not included in the analysis.

**Effects of acupoint hot compress during early puerperium on parturients after a vaginal delivery: study protocol for a randomized clinical trial**

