## 7. Subgroup analysis

To consider the potential effects of labor analgesic drug use on the outcomes, a subgroup analysis will be conducted according to whether medication is used for labor analgesia or not. The subgroup RRs and 95% CIs will be calculated together with interaction P values.

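### The primary analysis leaves out centre although equal arms per centre are planned, and the SAP does not say how a logistic model gives the reported RR or on which scale the subgroup interaction is tested

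*Supplement*

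**What the plan says.** - **SAP 5 (primary outcome).** The comparison of the two arms "will be performed using logistic regression model without any adjustment; relative risk (RR) and corresponding 95% confidence intervals(CIs) will be calculated". No log link, standardisation or other route from the logistic fit to an RR is named, there or in protocol section 7.
- **Protocol 2.4 (sample size).** "the estimated sample size is 600 cases in each group with 50 cases at each center in each group". Protocol 2.3.4 lists 12 hospitals; protocol section 11 says of two of them that "these two centers were not included in the trial".
- **Protocol 2.5 (randomisation).** Allocation is 1:1 from a list generated in R. Neither strata nor blocks are mentioned.
- **SAP 7 (subgroup by labour analgesia).** "The subgroup RRs and 95% CIs will be calculated together with interaction P values". No model is named for the interaction. SAP 9 adds that this subgroup was introduced after a preliminary look at the data suggested that spinal analgesia may affect the outcomes.
- **SAP 3 (missing data).** Multiple imputation will be used.

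**The concern.** Three things need settling.

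1. **Centre.** If equal numbers per arm at each centre are achieved by controlling allocation there, centre belongs to the design. The usual standard error for an unadjusted comparison then counts between-centre variation that the design has removed from the treatment contrast. The plan gives up a little precision that it could have at almost no cost.
2. **Effect measure.** The model named estimates an odds ratio and the measure reported is an RR. Retention is expected in about a quarter of controls, so the two differ visibly, and the step from one to the other is left to the analyst. Under multiple imputation there is no single two-by-two table to fall back on, so both the RR estimator and the scale for pooling need to be named.
3. **Interaction scale.** Equal RRs and equal ORs are different null hypotheses when baseline risk differs between subgroups. SAP 9 gives reason to expect such a difference by analgesia. The scale of the interaction test should therefore not be open.

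**Working it through.** **Inputs.** Protocol 2.4: "the incidence rate of urinary retention was 7.7% in the intervention group and 25.7% in the control group"; 50 per arm per centre. Protocol 2.3.4: 12 centres. The between-centre SD of the retention rate is not in the documents; 5 to 12 percentage points is assumed.

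**Plan's own figure.** 50 × 12 = 600 per arm and 600 × 2 = 1200, as stated. The stated rates, alpha and power do not lead to 600: the two-proportion formula gives 67 per arm, or 67/0.8 = 84 after 20% drop-out. That is a separate matter and nothing below depends on it. It does show that at the pilot rates power is above 99.99% with 400 to 600 per arm.

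**Does the quota imply control by centre?** Under simple 1:1 allocation of 100 women, P(exactly 50 per arm) = C(100,50)/2^100 = 0.080. Exact balance at every centre would therefore be unlikely without control by centre. The quota may, however, be only a target.

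**Cost of leaving out centre, if arms are balanced within centre.** The share of outcome variance due to centre is f = SD²/[p(1−p)], with p = 0.257 and p(1−p) = 0.257 × 0.743 = 0.191. The unadjusted interval is too wide by the factor 1/√(1−f), and the true two-sided size is 2[1 − Φ(1.96/√(1−f))].

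| Assumed centre SD | f | CI too wide by | True size at nominal 0.05 |
|---|---|---|---|
| 5 points | 0.0025/0.191 = 1.3% | 0.7% | 0.049 |
| 8 points | 0.0064/0.191 = 3.4% | 1.7% | 0.046 |
| 12 points | 0.0144/0.191 = 7.5% | 4.0% | 0.042 |

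A random centre intercept on the log-odds scale gives a similar picture: size 0.048 at SD 0.3 and 0.045 at SD 0.5. Only with much larger spread does it fall further, to 0.038 at SD 0.8 and 0.034 at SD 1.0.

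**OR against RR at the planning rates.**
- RR = 0.077/0.257 = 0.300.
- OR = (0.077/0.923)/(0.257/0.743) = 0.0834/0.3459 = 0.241.
- Read as relative reductions, these are 70% and 76%.

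**Can the RR be obtained from the planned fit?** Take 46/600 against 154/600, close to the planning rates. The logistic OR is 0.240 (95% CI 0.169 to 0.342). The RR is 0.299 (0.219 to 0.407) from a log-binomial model, from modified Poisson, and from the fitted logistic risks with a delta-method interval. All three routes agree.

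**Adding centre.** A common RR across centres keeps its value when centre is adjusted for. An OR does not: with a marginal OR of 0.241, the centre-conditional OR would be 0.237, 0.230, 0.214 and 0.201 for centre SDs of 0.3, 0.5, 0.8 and 1.0 on the log-odds scale. Simply adding centre to the logistic model would thus change the quantity estimated.

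**Interaction scale (illustrative risks).** Let RR = 0.5 in both subgroups, with control risks of 15% and 35%.
- OR = (0.075/0.925)/(0.15/0.85) = 0.459.
- OR = (0.175/0.825)/(0.35/0.65) = 0.394.
- Gap in log OR = ln(0.459/0.394) = 0.154.

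With 400 to 600 per arm and 30% to 70% of women in the lower-risk subgroup (assumed), the SE of that gap is 0.33 to 0.48. A 5% test on the OR scale would then reject 6.2% to 7.5% of the time although the RRs are identical.

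**The case against.** The strongest defence is that a pre-specified unadjusted comparison is valid and transparent and prevents selection of covariates after the fact. With arm as the only term the logistic model is saturated: OR = 1 exactly when RR = 1, and the RR from its fitted risks is the crude risk ratio. All of that stands. The planned primary test is valid, and what is at stake over centre is efficiency.

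Three stronger readings are tempting, and the documents do not support them.

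- *The plan will overstate the benefit.* A reader might infer this from the pairing of a logistic model with an RR. SAP 5 says that an RR will be calculated; it nowhere says that an odds ratio will be reported as one. The figures 0.24 and 0.30 show what a mislabelling would cost, and do not show that one is planned.
- *Randomisation was stratified by centre.* The 50 per arm per centre stands in the sample-size section and can be read as a recruitment target. Protocol 2.5 is silent on strata and blocks. If the list was not controlled by centre, the unadjusted test has its nominal size and the interval is not too wide for the design.
- *The subgroup P value comes from a logistic interaction.* SAP 7 names no model, so the test could already be on the RR scale. Even on the OR scale, the distortion in the example is small.

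What remains against the plan is that it excludes adjustment for a factor it intends to balance, and leaves open the estimator of the RR and the scale of the interaction.

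**Conclusion.** The point holds as an inexpensive improvement and a clarification; it does not make the primary analysis invalid. If allocation was controlled by centre, leaving centre out makes the 95% CI about 0.7% to 4% too wide and lowers the true size from 0.05 to between 0.049 and 0.042, with no bias in the marginal RR. This rests on assumed centre SDs of 5 to 12 points. At the pilot effect the trial's conclusion would not depend on it; it matters somewhat more if the true effect is smaller. The gap between OR 0.24 and RR 0.30 follows from the plan's own rates and is reason enough to name the RR estimator. The interaction scale is unspecified; choosing the OR scale would change the null being tested, with a modest effect on error rates in the example.

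**What to change.** - **SAP 5.** Estimate the RR and the risk difference with 95% CIs, taking account of centre. For the RR, use either a modified Poisson model (log link, robust standard errors) with arm and centre, or a centre-stratified Mantel-Haenszel estimate. Keep the unadjusted RR as a sensitivity analysis. State that imputed datasets are pooled on the log-RR scale.
- **SAP 7.** Test arm by analgesia in the same log-link model, so that the interaction P value and the subgroup RRs refer to one scale.
- **Protocol 2.5.** State whether the list was stratified or blocked by centre. The text should report what was done; it should not assert stratification because the quota suggests it.

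The cost is a few sentences of SAP text, a few lines of R, and a primary model slightly more complex than a two-by-two comparison. No further data are needed beyond each woman's centre.

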## 6. Analyses for Secondary Outcome

For the secondary outcomes, the changes of postpartum uterine contraction pain assessing with Visual Analogue Scale Score at  $6\pm0.5$ ,  $28\pm0.5$ ,  $52\pm0.5$  and  $76\pm0.5$  hours after birth will be analyzed by fitting a linear mixed model using treatment, time, treatment by time interaction as a fixed effect, the comparison between the two groups at each time-point will be performed using linear regression model.

The emotion symptoms screening by the Edinburgh Postnatal Depression Scale Score will be compared using a logistic regression model.

The lactation initiation time will be compared using the Wilcoxon rank-sum test. The changes of breastfeeding milk volume, feeding mood and feeding times at  $28\pm0.5$ ,  $52\pm0.5$  and  $76\pm0.5$  hours after birth will be analyzed by a generalized linear mixed model. The difference of breast feeding milk volume and feeding times between two groups at each time-point will be analyzed by an ordinal logistic regression model, and feeding mood will be analyzed by a logistic regression model. The changes of newborn weight at  $28\pm0.5$ ,  $52\pm0.5$  and  $76\pm0.5$  hours after birth will be analyzed by fitting a linear mixed model using treatment, time, treatment by time interaction as a fixed effect, the comparison between the two groups at each time-point will be performed using a linear regression model.

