### **2.3.3 Trial design**

The study is a prospective, multi-center, and randomized controlled clinical trial, which will be conducted in China. All enrolled subjects will be comprehensively briefed on the study, including the purpose, procedure, and possible risks of the study. Informed consent will be obtained from all participants before the start of this study. The demographic data, information about pregnancy, delivery, and newborns will be recorded as baseline data. When the protocol need to be modified, the implementation will be started only after the corresponding revised parts approved by the ethics committee, and all research centers, investigators and the funder are notified at the same time. The study will follow the Code of Ethics of the World Medical Association (Declaration of Helsinki). This protocol is compliant with the Standard Protocol Items: Recommendations for Interventional Trials (SPIRIT) statement (Figure 1) and the Consolidated Standards of Reporting Trials (CONSORT) guidelines (Figure 2).

|                                                    | STUDY PERIOD |            |                               |                      |                      |                               |                                |                                |                                |
|----------------------------------------------------|--------------|------------|-------------------------------|----------------------|----------------------|-------------------------------|--------------------------------|--------------------------------|--------------------------------|
|                                                    | Enrolment    | Allocation | Post-allocation               |                      |                      | Follow-up                     |                                |                                |                                |
| TIMEPOINT
(after delivery)                      | - $t_1$      | 0          | $t_1$
Within 30
minutes | $t_2$
24
hours | $t_3$
48
hours | $t_4$
6 $\pm$ 0.5
hours | $t_5$
28 $\pm$ 0.5
hours | $t_6$
52 $\pm$ 0.5
hours | $t_7$
76 $\pm$ 0.5
hours |

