### 2.8.2 Secondary outcomes

Postpartum uterine contraction pain: The visual analogue scale (VAS) will be used to evaluate the postpartum uterine contraction pain intensity: Using a horizontal ruler of 100 mm, “0” representing no pain and “100” representing unbearable pain. The pain VAS intensity will be respectively measured at  $6 \pm 0.5$  hours,  $28 \pm 0.5$  hours,  $52 \pm 0.5$  hours, and  $76 \pm 0.5$  hours after delivery.

Emotion symptoms: The Edinburgh Postnatal Depression Scale (EPDS) will be used for screening the depressive symptoms at  $76 \pm 0.5$  hours after delivery. It contains 10-item: pessimism, lack of interest, self-blame, worry, fear, impaired ability, sleep disorder, sadness, tearfulness, self-injury/suicidal ideation, each of which is scored from 0 to 3.

Lactation: The lactation initiation time will be recorded, and the breastfeeding milk volume, feeding mood and times, and the newborn weight will be measured at  $28 \pm 0.5$ ,  $52 \pm 0.5$ , and  $76 \pm 0.5$  hours after delivery, respectively. The breastfeeding milk volume is measured as “-” to “++++”: no milk outflow during finger extrusion(-); milk occasionally flows out during finger extrusion, which cannot meet the needs of the infants (+); milk flows out slowly when squeezed by fingers but does meet the needs of infants (+ +); milk continuously flows out during finger extrusion, which can meet the needs of infants (+ + +); there is milk flowing out in a jet shape when the nipple is squeezed by the fingers, which can meet the needs of infants (+ + + +).

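### SAP 6 compares newborn weight at 28, 52 and 76 hours without birth weight as a covariate, which costs precision in the between-group contrasts

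*Supplement*

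**What the plan says.** SAP 6 (Analyses for Secondary Outcome) introduces the endpoint with "The changes of newborn weight at" 28, 52 and 76 hours and states that it "will be analyzed by fitting a linear mixed model using treatment, time, treatment by time interaction as a fixed effect". The same phrase appears earlier in that section for pain; the second occurrence is the one meant here. The section then says that "the comparison between the two groups at each time-point will be performed using a linear regression model". No covariate is named in either model, and no random effect is described.

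Newborn weight is also a baseline item. Protocol 2.3.3 says: "The demographic data, information about pregnancy, delivery, and newborns will be recorded as baseline data". SAP 4 lists "Newborn weight; Newborn length; Apgar score", and Protocol 2.7 names the same three items. Neither list uses the term birth weight. However, the entry sits beside length and Apgar score and carries no time window, whereas the postpartum diet and appetite items in the same lists do. The follow-up weights are set out separately under lactation in Protocol 2.8.2: "and the newborn weight will be measured at" the three later times. It is therefore reasonable to take the baseline entry as weight at birth.

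**The concern.** The same infant is weighed at birth and again within about three days, so later weight should depend strongly on birth weight. Promoting lactation is one of the stated objectives (Protocol 2.3.1), and newborn weight is listed under lactation. An effect of the compress on feeding would appear as a shift in early weight change, which is likely to be small beside the spread of birth weights. A comparison of raw weights leaves that spread in the residual. The compress starts only after delivery, so birth weight is a legitimate covariate, and it is already collected. At stake is whether a null result on this outcome would say much about modest effects.

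**Working it through.** **The plan's own figures.** The documents give no SD, correlation, power or precision for newborn weight, so there is nothing to reproduce for this outcome. The only calculated size is for urinary retention, where "the incidence rate of urinary retention was 7.7% in the intervention group and 25.7% in the control group" in the pilot. With one-sided 0.025 and 80% power:

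n = [1.960 × √(2 × 0.167 × 0.833) + 0.842 × √(0.077 × 0.923 + 0.257 × 0.743)]² / 0.18² = 67 per arm, or 67/0.8 = 84 after 20% drop-out.

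The stated 600 per arm is 12 centres × 50, not the output of this formula. That does not bear on the present point, which needs only the number per arm.

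**Inputs**
- Infants per arm: 500, from 10 centres × 50. Protocol 2.4 gives 50 per centre per arm, and Protocol section 11 says two of the 12 centres were not included. That the other ten keep 50 each is an assumption.
- Test level: "All hypothesis testing will be carried out at the 5% (2-sided) significance level" (SAP 2).
- SD of newborn weight: 400 g, assumed; range 350 to 450 g.
- Correlation ρ of birth weight with later weight: 0.90 to 0.98, assumed; 0.80 shown as a pessimistic case.

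**Raw comparison at one time-point**
- SE = SD × √(2/n) = 400 × √(2/500) = 25.3 g
- Detectable difference at 80% power = (1.960 + 0.842) × 25.3 = about 71 g

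**With birth weight as covariate:** SE = 25.3 × √(1 − ρ²)

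| ρ | √(1 − ρ²) | SE (g) | Detectable (g) | SE ratio, raw/adjusted | Variance ratio |
|---|---|---|---|---|---|
| 0.80 | 0.600 | 15.2 | 42.5 | 1.7 | 2.8 |
| 0.90 | 0.436 | 11.0 | 30.9 | 2.3 | 5.3 |
| 0.95 | 0.312 | 7.9 | 22.1 | 3.2 | 10.3 |
| 0.98 | 0.199 | 5.0 | 14.1 | 5.0 | 25.3 |

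The ratios depend on ρ alone. The grams move with SD and n, for ρ from 0.90 to 0.98:
- SD 350 g: 62 g raw, 27 to 12 g adjusted.
- SD 450 g: 80 g raw, 35 to 16 g adjusted.
- SD 400 g and 400 per arm (500 less 20%): 79 g raw, 34.5 to 15.8 g adjusted.

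**Simulation check.** One simulated trial per setting, 500 per arm, birth-weight SD 400 g, subject random intercept:

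| Assumed SD of change from birth (g) | ρ at 76 h | SE at 76 h, raw → adjusted (g) | Ratio |
|---|---|---|---|
| 80 | 0.98 | 25.6 → 5.0 | 5.1 |
| 100 | 0.97 | 25.9 → 6.3 | 4.1 |
| 150 | 0.93 | 26.4 → 9.6 | 2.8 |

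In the mixed model at change SD 80 g, the SE of the treatment term fell from 25.5 to 5.1 g. The SE of the treatment by time interaction (76 against 28 hours) was 4.29 g with and without birth weight. That contrast is within infant, so birth weight already cancels.

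**If the outcome were change from birth weight.** With equal variances at the two times, the change score has variance proportional to 2(1 − ρ) and the adjusted analysis to 1 − ρ². The ratio is 2/(1 + ρ) = 1.05, 1.03 and 1.01 at ρ = 0.90, 0.95 and 0.98. Nearly all the gain would then already be there.

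**The case against.** The strongest reply is that SAP 6 speaks of changes in newborn weight. If that means change from the recorded birth weight, only 1 to 5% of efficiency is at stake. This cannot be excluded. But the same section uses the word for pain, milk volume, feeding mood and feeding times, none of which has a value at birth. It therefore reads more naturally as change across the listed follow-up times. Either way the SAP should say which is meant.

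Several stronger readings are tempting, and the documents do not support them:
- A reader might infer that the whole newborn-weight analysis is weakened. It is not: given a subject random effect, the interaction loses nothing. It does, however, address only divergence after 28 hours, so it does not replace the time-point contrasts.
- A reader might infer that a chance imbalance in birth weight biases the result. Under 1:1 randomisation, with all randomised women analysed (SAP 1), the unadjusted contrast is unbiased. Its standard error already allows for such imbalance, and the type I error is held.
- A reader might infer that weight change over the first day is never assessed. On the raw reading it is not modelled directly. Still, the arms share the same expected birth weight, so the 28-hour contrast targets the same effect, only less precisely.
- A reader might take the variance ratios of 5 to 25 as established. They rest on assumed correlations. On the SE scale, a ratio of 3 or more needs ρ of about 0.94.

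It also stands that newborn weight is one of several lactation measures and that the trial was not sized on it.

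**Conclusion.** The point holds as a loss of precision in one secondary outcome. On the likelier reading that raw weights are modelled, the treatment main effect and the contrasts at 28, 52 and 76 hours have standard errors about 2.3 to 5 times larger than they need be. This rests on an assumed ρ of 0.90 to 0.98. The figures in grams rest further on SD 400 g and 500 per arm. None of these assumptions comes from the documents except the 50 per centre and the removal of two centres. Even at ρ = 0.80 the SE ratio is 1.7. No conclusion of the trial becomes invalid, and the primary outcome is untouched. The case for acting is that the improvement is specific and uses data already collected.

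**What to change.** In SAP 6, for newborn weight:
1. State whether the outcome is weight at each follow-up time or change from birth weight.
2. Add birth weight and birth weight by time to the fixed effects of the mixed model, and name a subject random effect. The product term lets the slope on birth weight differ between 28 and 76 hours.
3. Take the 28, 52 and 76-hour contrasts from that model, or else add birth weight to each time-point regression.
4. In SAP 4 and Protocol 2.7, label the baseline item as weight at birth.

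The calculated gain comes from birth weight alone; no further covariates are needed for it. The cost is a few lines of SAP text and no new data. If weights have already been compared by arm, report the adjusted analysis as a later addition, beside the unadjusted one.

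### SAP 6 puts the 0–30 EPDS into a binary logistic model with no cut-off, and has no rule for women whose lactation has not started by 76 hours

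*Supplement*

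**What the plan says.** **EPDS.** Protocol 2.8.2 says that the scale "will be used for screening the depressive symptoms at" 76 ± 0.5 hours, with ten items, "each of which is scored from 0 to 3". It states neither the total nor a threshold. SAP 6 gives the whole analysis in one sentence: "The emotion symptoms screening by the Edinburgh Postnatal Depression Scale Score will be compared using a logistic regression model". In the same section, milk volume and feeding times "will be analyzed by an ordinal logistic regression model", so the SAP names the ordinal form where it means it. Plain logistic for the EPDS reads as binary.

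**Baseline mood.** Protocol 2.7 and SAP 4 list four mood items, among them "Little interest or pleasure in doing things; Feeling down, depressed, or hopeless"; the other two cover nervousness and uncontrolled worry. SAP 4 summarises and tests them at baseline. SAP 6 gives them no part in the EPDS comparison.

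**Lactation initiation.** Protocol 2.8.2 says that the time is recorded. SAP 6 says: "The lactation initiation time will be compared using the Wilcoxon rank-sum test". The last assessment is at 76 ± 0.5 hours (Protocol Figure 1, 2.8.2 and section 11). The lowest milk-volume grade, "no milk outflow during finger extrusion", is available at all three lactation visits, including the last. Neither document gives a code or rank for a woman who has not started by then. The only general rule for absent values is SAP 3: "Missingness is considered to be missing at random (MAR) and multiple imputation (MI) techniques will be used for handling missing data".

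**The concern.** Protocol 2.3.1 names preventing emotional disorders and promoting lactation as objectives, so each of these two analyses carries a stated aim of the trial.

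For the EPDS, a binary model without a cut-off leaves the endpoint undefined. Someone must choose the event, and the documents do not require the choice to be made before data are seen. Any split also discards the differences between scores on the same side of it.

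For lactation, a woman still without milk at the last visit has no time to record. If the blank field fell under SAP 3, she would be given a time modelled on women who did start, although hers is known to be longer than 76 hours. That would remove part of any contrast in late starting.

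**Working it through.** The documents give no power, effect size or distribution for either outcome, so there is no planned figure to reproduce. From the documents: 600 per group and 20% drop-out (Protocol 2.4), hence 600 × 0.8 = 480 per arm; two-sided 5% (SAP 2); EPDS maximum 10 × 3 = 30. The score and time distributions below are assumptions.

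**1. Efficiency of a split, normal score.** With a proportion p above the cut and c the matching normal quantile, efficiency relative to the full score is φ(c)²/[p(1−p)]. At p = 0.10: 0.1755²/0.09 = 0.34. At p = 0.20: 0.280²/0.16 = 0.49. A comparison with 80% power on the score falls to Φ(2.80√0.342 − 1.96) = 37% and Φ(2.80√0.490 − 1.96) = 50%.

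**2. The same, skewed score.** Assume a negative binomial with k = 2.2 and means 6.0 and 5.25.
- Variances (μ + μ²/k): 6 + 36/2.2 = 22.4 and 5.25 + 27.6/2.2 = 17.8.
- Full score: z = 0.75/√(40.1/480) = 2.59, so power is Φ(2.59 − 1.96), about 73–74%.
- Cut at ≥9: 24.2% against 18.7% positive, z about 2.07, efficiency (2.07/2.59)² = 0.64.

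| Cut-off | Efficiency, skewed model | Efficiency, normal formula at the same prevalence | Simulated power of the split |
|---|---|---|---|
| ≥9 | 0.64 | 0.51 | 55% |
| ≥10 | 0.61 | 0.45 | 51% |
| ≥12 | 0.53 | 0.35 | 48% |
| ≥13 | 0.48 | 0.30 | 43% |

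In the same 3,000-run simulations the whole score had about 73% power by t test and about 67% by a rank test.

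**3. Choosing the cut-off afterwards.** With no true difference (both means 6.0; 20,000 runs), each single cut-off from ≥9 to ≥13 holds about 5%. The chance that at least one of the five is significant is 12.9%; for ≥9, ≥10 and ≥13 only, it is 10.6%. These are the error rates if the most favourable cut-off is taken.

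**4. Lactation.** Assume log-normal times, log-SD 0.5, time ratio 0.92, 480 per arm, follow-up cut at 76 h. Power by handling:

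| Control median | Controls not started by 76 h | Full follow-up | Wilcoxon, tied last | Log-rank | Not-started women excluded |
|---|---|---|---|---|---|
| 30 h | 3% | 72% | 72% | 66% | 65% |
| 45 h | 15% | 70% | 70% | 64% | 46% |
| 60 h | 32% | 72% | 69% | 64% | 32% |

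Exclusion also shrinks the difference in medians. At a control median of 45 h it goes from 45.0 − 41.4 = 3.6 h to 41.0 − 38.6 = 2.4 h.

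**5. Imputation instead of exclusion.** In another assumed scenario (medians 48 and 44 h, log-SD 0.5, 500 per arm, ten within-arm imputations, 1,000 runs), power was 76% tied last, 50% with exclusion and 48% with imputation under missing at random. Imputation does not recover what exclusion loses.

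**The case against.** **A binary EPDS suits the purpose.** The protocol uses the scale for screening, and a screen-positive proportion fits the aim of preventing emotional disorders. This stands as a reason to report a split. It does not supply the missing cut-off, and it does not require the split to be the only analysis.

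**The statisticians are blinded.** Protocol 2.5 says so, and this limits a choice driven by the treatment difference. It does not close the gap. SAP 9 records that a subgroup analysis was added after a preliminary look at the data, so the plan was still open to change at that stage. A reader might infer that a cut-off was, or will be, picked to suit the result. The documents do not show that; they only leave it possible.

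**The loss from splitting depends on the score's shape.** This stands. A reader might infer from the normal formula that most of the information goes. Under the skewed model three of the four cut-offs keep more than half.

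**An unadjusted comparison is valid.** True: SAP 5 leaves even the primary outcome unadjusted. Adjustment for baseline mood is a gain in precision, not a correction of bias. Its size cannot be computed, because the documents give no correlation with the EPDS.

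**The plan does not treat late women as missing.** Correct. A reader might infer it from SAP 3, but that section does not classify them, and ranking them last is equally open. Nor does the Wilcoxon test itself waste information: with late women tied last it lost at most 3 percentage points against full follow-up and beat log-rank in all three scenarios. The bottom milk grade allows for women not started at 76 h but does not show that there are any.

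**Conclusion.** Two gaps hold, both in secondary analyses.

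The EPDS gap is the firmer. A 0–30 score enters a binary model with no event defined in either document. Under the assumed skewed distribution, the type I error could reach about 13% if the best of five cut-offs were taken, and a split gives 43–55% power where the whole score gives about 73%. Across both distributions and the four cut-offs tabulated, efficiency is roughly 0.3 to 0.65. The direction of the loss holds in both models; its size rests on assumptions that the documents cannot confirm.

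The lactation gap is a missing coding rule, not a wrong test. Missing at random cannot describe a woman whose time is known to exceed 76 h, so SAP 3 would be wrong if applied to her. The cost depends on a share that the documents do not give: it is modest at 3% of controls (72% to 65% if such women are excluded) and large at 32% (69% to 32%). The documents do not support saying that the plan drops or imputes these women, or that the Wilcoxon test must be replaced by log-rank or Cox.

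**What to change.** **EPDS, SAP 6.** Make the total score the main analysis, by linear or proportional-odds regression, adjusted for the four baseline mood items. Protocol 2.7 gives no time for these items, so confirm that they were recorded before allocation. Keep one cut-off as a supportive screen-positive analysis by logistic regression, and write it into the SAP now.

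**Lactation, SAP 6 and SAP 3.** Keep the Wilcoxon test. State that women seen at the 76-hour visit whose lactation has not started are ranked tied last at one common cut-off time, and are excluded from imputation. Women lost before that visit stay under SAP 3. Report the number not started in each arm.

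**Cost.** SAP wording only, with no new data. The one real drawback is that a difference in mean EPDS, or a proportional odds ratio, is less familiar to clinicians than a percentage above a threshold; the supportive analysis supplies that percentage.
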